#### Interim analysis

A single interim analysis of efficacy will take place when half of the patients have completed follow-up. The trial will use the Peto approach [37] whereby the criterion for statistical significance at the interim analysis will be set at *p* < 0.001, and the criterion at the final analysis will be set at p < 0.05, which will maintain an overall α = 0.05. The Data Safety Monitoring Committee (DSMC) will use this guideline in combination with data on toxicity and secondary outcomes to decide whether to recommend continuation or termination of the trial.

Any deviations from the original statistical plans will be described and justified in an amendment to the protocol and/or in the final report, as appropriate.

### Safety assessment

The DSMC, consisting of one radiation oncologist, one medical physicist, and one biostatistician, will review data relating to safety and efficacy. The DSMC will conduct and review interim analyses and ensure the continued scientific validity and merit of the study. There will be one interim review conducted by the DSMC as described above.

Safety will be monitored through therapist daily interactions with the patient while on treatment, skin assessments, and PRO. NCI CTCAE V4.0 scores below grade 4 are expected in both arms. Adverse events (AEs) and severe adverse events (SAEs), as defined by the International Conference on Harmonization (ICH) [38], will be detected by the treating therapist at the time of treatment or follow-up assessment, or reported by the patient. Examples of adverse events (AEs) are skin reactions above grade 3, a treatment unit collision with the patient, or a patient fall during treatment setup. A PRO “yes” response to Q11 indicating the patient requires additional support to manage treatment related changes in skin will trigger a follow-up phone call to the patient to determine if an AE has occurred and provide the patient with appropriate management. The investigator and qualified designees will remain responsible for following up on AEs that are serious, considered related to the study intervention or study procedures, or that caused the participant to discontinue the study intervention. After the initial AE/SAE report, the investigator will proactively follow each participant at subsequent visits/contacts. All SAEs will be followed until resolution, stabilization, the event is otherwise explained, or the participant is lost to follow-up.

All SAEs and AEs will be collected from the start of intervention until the last follow-up visit. All SAEs will be recorded and reported to the sponsor or designee immediately, prior to the next scheduled treatment, or if treatment is complete, within 24 h. Any updates to SAE data will also be submitted to the sponsor within 24 h. The trial will be discontinued if a significantly higher rate of SAE is observed for the experimental arm versus the control arm, or upon recommendation by the DSMC at the time of the interim analysis.

For routine toxicity management, any dose interruptions or dose reductions in either arm (at the discretion of the radiation oncologist) will be monitored throughout the study. All interruptions or reductions will be documented in the patient’s treatment record and noted on the subsequent skin assessment form. Our standard institutional policies and procedures for pregnancy will be followed in this study.

### Confidentiality and data storage

Participants will be assigned a unique identifier by the study sponsor. Any participant records or datasets that are transferred to the sponsor will contain the identifier only; participant names (or other identifying information) will not be transferred. The participant will be informed that their personal study-related data will be used by the sponsor in accordance with local data protection laws. The level of disclosure will also be explained to the participant who will be required to give consent for their data to be used as described in the informed consent form (ICF). The participant will be informed that their medical records may be examined by Clinical Quality Assurance auditors or other authorized personnel appointed by the sponsor, by appropriate research ethics board (REB) members, or by inspectors from regulatory authorities.

All participant data relating to the study will be recorded on printed forms or in electronic format for upload into a restricted-access database housed on secure hospital servers (RedCap). Database entry will occur at the coordinating study site. For other sites, printed data forms should be scanned and emailed to the coordinating site within two weeks of the last assessment for each patient. Original copies will be retained at the treating centres. Digital copies of data collection forms, as well as any photographs taken for skin assessments, will be stored on a secure server accessible only to study staff. Database access will be restricted to the study monitor and any staff who will be entering data. The case report form (CRF) will be reviewed for accuracy and signed off by the study physicist and/or lead study therapist at the treating centre prior to data entry.

Source data for treatment planning, imaging, and setup will be retained in our institutional Aria™ Radiation Therapy clinical database, per standard of care for all patients. Source data for PRO data will be retained in the PRO database and may be uploaded into the RedCap database for analysis. A regular backup of the study databases will be performed.

Records and documents pertaining to the conduct of this study, including signed ICFs, will be retained by the investigator for 25 years after study completion. No records will be destroyed during the retention period or transferred to other locations or parties without the written approval of the sponsor. At the close of the study, the study coordinator will collect all study-related data from participating centres to be stored in a single location.

### Informed consent

Pre-screening for eligible patients who have an IMF skin fold and/or lateral ptosis in supine positioning will be done by the attending radiation oncologist or study therapist at the new patient assessment appointment. The study will be discussed at this appointment and participants will be informed that their participation is voluntary. The investigator or delegate will explain the nature of the study to the participant (or a legally authorized representative for the participant, as appropriate) and answer all questions regarding the study.

Voluntary, written, dated, and signed ICFs for participation in the study will be obtained prior to performing any study-related procedures. The radiation oncologist, study therapist, or study coordinator will provide ICFs to potential participants allowing adequate time for review prior to the CT simulation appointment. The ICF will meet the requirements of the REB and study center. The authorized person obtaining the informed consent must also sign and date the ICF. A copy of the ICF will be provided to the participant.

Screening evaluations will be completed and reviewed to confirm that participants meet all remaining eligibility criteria prior to enrolment. A screening log will be maintained to record details of all participants screened, to confirm eligibility, and to record reasons for screening failure, as applicable. The medical record will include a statement that written informed consent was obtained before the participant was enrolled in the study and the date the written consent was obtained.

Extension of this study to look at longer-term toxicities of breast RT including cosmesis, secondary cancer induction, recurrence, skin, lung, and heart toxicity is under consideration. Patients will be asked if they consent to having their data used in subsequent analysis.

### Participant withdrawal

A participant may withdraw from the study for any reason at any time. Patients may also be withdrawn from the study at the discretion of the investigator and/or treatment team, for example, if problems arise with healing of the surgical wound if this interferes with the required skin assessments or causes treatment interruption or delay. Participants withdrawn from the study shall continue to receive appropriate treatment as decided upon with their radiation oncologist. Data collected up to the point of withdrawal will remain in the study.

Patients in the control arm who withdraw from the study post-CT simulation will continue with treatment as planned, with no interruption. Patients in the experimental study arm who withdraw from the study will decide, in discussion with the treating oncologist, whether to continue with CARA or to change to the standard of care breast positioning method. In the latter case, the patient will be required to undergo repeat CT simulation and planning with the standard method. This process typically requires one week and may be done currently with continued treatment with CARA if desired. Otherwise, a treatment interruption may be required.

A participant is considered to have completed the study if they have completed all phases of the study including treatment and the final PRO questionnaire. If a participant fails to complete a follow-up PRO assessment, the site will attempt to contact the participant weekly and counsel the participant on the importance of maintaining the assigned follow-up schedule and ascertain whether the participant wishes to and/or should continue in the study. Should the participant remain unreachable out to eight weeks from the start of RT, they will be considered to have withdrawn from the study.

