#### Patient-reported outcomes

The PRO questionnaire will be provided on tablets in the clinic by the study radiation therapist on the days that the patient is being assessed and by e-mail post-RT.Secondary patient-reported outcomes include severity of fatigue, pain, sleep interruption, activity interruption, comfort during the treatment procedure, and use of steroid cream or analgesics.

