#### Staff skin assessments

Staff radiation therapists, nurses, or radiation oncologists blinded to the treatment arm will perform skin assessments. Staff performing these assessments are required to undergo specific training for this purpose. An in-house MD scoring tool specifically for the IMF will be used in addition to CTCAE V4.0 skin toxicity criteria. Staff skin assessments are required at baseline and during the last week of treatment (or in five-fraction prescriptions, required on the last day of treatment). If the patient is able and willing, staff skin assessments will also be completed weekly thereafter, out to 7 weeks after the start of breast RT.

Each staff skin assessment includes taking photographs of the treated skin in the IMF. Photos of other areas of skin experiencing MD at the time of each assessment may also be acquired. For patients assessed remotely, the patient may be asked to provide photographs of their skin taken at the time of the assessment.

While the method of breast positioning (i.e., Arm 1 or Arm 2) will be open label to the patient and treating staff, it is preferred that staff performing the follow-up skin assessments be blind to which arm of the study participants are in and not have access to the randomization allocation data. If this is not possible (such as in smaller centres), one additional trained study member will perform blinded assessment using photographs taken of the treated IMF area. If there is disagreement between the two assessments, a third trained study member will perform blinded assessment using the photographs. The final assessment of the primary outcome will be by majority vote.

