### Statistics and analysis

#### Sample size calculation and recruitment period

Based on evidence from previous studies [5–8], we expect a control arm rate of 50% for any degree of MD in the IMF. Due to a reduction in skin folds and reduction in V105% with reduced breast separation, we hypothesize a rate of 30% moist desquamation in the study arm (i.e., an absolute decrease in incidence of 20%). For this effect size with 80% power and two-tailed α = 0.05, the sample size is 93 patients in each arm. Because of the nature of the study and 10% observed loss to follow-up in our pilot study, we will enroll 110 patients in each arm.

We expect that a 3-year recruitment period will be sufficient for the trial. A similar multicentre study from our team [5] achieved a similar recruitment rate in the same patient population drawing from only two centres.

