#### *Statistical methods – *primary* outcome*

The proportion of patients experiencing MD in the IMF in the two arms will be compared using logistic regression to assess the effect of treatment, adjusting for brassiere cup size, skin fold size, BMI, smoking status, and dose fractionation schedule. An unadjusted comparison will also be made using the chi-square test, or Fisher’s exact test, if appropriate. Those participants who do not complete all follow-up but have reported MD are included in the analysis. Those who do not complete all follow-up and do not report MD will be excluded from the primary analysis. A sensitivity analysis including those lost to follow-up will be done using multiple imputations for missing data.

Baseline descriptive variables (e.g., age, smoking status, BMI, as described in the section Baseline Assessment) will be compared descriptively between the two arms of the study and assessed for imbalance. Formal statistical comparisons of baseline characteristics in RCTs are not advised [35].

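### Open-label staff may withdraw randomised women at discretion, no outcome follow-up is stated afterwards, and the primary analysis then drops those who have not reported moist desquamation

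*Protocol article*

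**What the plan says.** Four statements in the protocol article combine here.

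- **Participant withdrawal.** Apart from withdrawal by the patient herself: "Patients may also be withdrawn from the study at the discretion of the investigator and/or treatment team". One example is given: trouble with healing of the surgical wound, where it gets in the way of the skin assessments or leads to interrupted or delayed treatment. As this is only an example, the grounds are open. Data up to withdrawal are retained; nothing is said about collecting the outcome afterwards. Completing the study requires the final patient-reported outcome (PRO) questionnaire.
- **Staff skin assessments.** The positioning method "will be open label to the patient and treating staff". Blinding is preferred for the staff who do the follow-up skin assessments.
- **Statistical methods – primary outcome.** Women with incomplete follow-up who have reported MD are kept. For the others: "Those who do not complete all follow-up and do not report MD will be excluded from the primary analysis". A sensitivity analysis with multiple imputation covers those lost to follow-up.
- **Patient-reported outcomes (secondary endpoints and measures).** The questionnaire is given on tablets "on the days that the patient is being assessed and by e-mail post-RT". The PRO section under Data collection also allows remote completion with help from blinded staff.

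**The concern.** Read together, these rules allow people who know the allocation to decide, after randomisation, that a woman leaves the study, and her leaving removes her from the primary analysis if MD has not yet been reported. The primary comparison is protected by randomisation only if such removals are unrelated to arm and to prospective MD risk. The plan secures neither.

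Two features make imbalance conceivable, though they do not show that it will occur. First, the same section gives withdrawal different consequences by arm: a control patient carries on as planned, while a CARA patient may change to standard positioning after repeat simulation. Second, the Patient population section starts weekly questionnaires in the last week of treatment, whereas Table 1 has them weekly during radiotherapy. On the first reading, a woman withdrawn earlier has had no on-treatment questionnaire on which to report MD, so she would be excluded.

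At stake is bias in the primary estimate rather than power.

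**Working it through.** **Inputs from the protocol (Sample size calculation and recruitment period).** Control rate: "we expect a control arm rate of 50% for any degree of MD in the IMF". Experimental rate: "we hypothesize a rate of 30% moist desquamation in the study arm". Size: "For this effect size with 80% power and two-tailed α = 0.05, the sample size is 93 patients in each arm". Inflation: "10% observed loss to follow-up in our pilot study, we will enroll 110 patients in each arm".

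**Step 1: reproduce the plan's figure.** With pooled variance under the null and no continuity correction,

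n = [1.960·√(2·0.4·0.6) + 0.842·√(0.5·0.5 + 0.3·0.7)]² / 0.2² = (1.358 + 0.571)² / 0.04 ≈ 93 per arm.

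This agrees with the protocol. Then 93/0.9 = 103.3, that is 104, so 110 leaves some room. Power at 50% versus 30% is about 86% with 110 per arm and 82% with 99 per arm (10% dropped). The sample size is not in dispute.

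**Step 2: five women lost from one arm.** Assume all five would have had MD, none had reported it before withdrawal, and the other arm loses nobody.

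- Five control women: 55/110 becomes 50/105 = 47.6%; difference 47.6 − 30.0 = 17.6 points.
- Five CARA women: 33/110 becomes 28/105 = 26.7%; difference 50.0 − 26.7 = 23.3 points.

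**Step 3: withdrawal as a fraction of each arm.** The protocol gives no withdrawal rate by arm and no MD risk among the withdrawn. The fractions below and the 80% risk are assumptions. When withdrawal precedes any report of MD, the observed rate in an arm is

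(110·p − 110·w·r) / (110·(1 − w)),

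where p is the true rate, w the fraction withdrawn and r the MD risk among them.

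| True rates, control / CARA | Withdrawn, control / CARA | Risk r | Observed, control / CARA | Difference (true value) |
|---|---|---|---|---|
| 50% / 50% | 0% / 10% | 80% | 50.0% / 46.2/99 = 46.7% | 3.3 (0) |
| 50% / 50% | 5% / 15% | 80% | 50.6/104.5 = 48.4% / 41.8/93.5 = 44.7% | 3.7 (0) |
| 50% / 30% | 5% / 15% | 80% | 48.4% / 19.8/93.5 = 21.2% | 27.2 (20) |
| 50% / 30% | 15% / 5% | 80% | 44.7% / 28.6/104.5 = 27.4% | 17.3 (20) |
| 50% / 50% | 10% / 10% | 80% | 46.7% / 46.7% | 0 (0) |
| 50% / 30% | 10% / 10% | 80% | 46.7% / 24.2/99 = 24.4% | 22.2 (20) |

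By a normal approximation to the unadjusted chi-square test, the two-sided rejection probability under no effect is about 7.7% in the first row and 8.2% in the second, instead of 5%.

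**Step 4: the opposite mechanism.** Suppose the withdrawn have average risk and every MD among them is reported before they leave. Only MD-free women are then dropped. With no true effect and 5% control versus 15% CARA withdrawn: control 55/(110 − 5.5·0.5) = 55/107.25 = 51.3%; CARA 55/(110 − 16.5·0.5) = 55/101.75 = 54.1%. That is a spurious 2.8 points against the device.

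The sign therefore depends on which arm loses more women, on their risk, and on whether MD was reported before they left.

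**The case against.** A reader might infer that the resulting bias is beyond remedy. The protocol does not support that: the sentence after the exclusion rule plans multiple imputation for those lost to follow-up. This safeguard stands, with limits. It is a sensitivity analysis, whether staff-withdrawn women count as lost to follow-up is not stated, and imputation relies on assumptions that discretionary removal by arm-aware staff may break.

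A reader might also infer that treatment interruption is itself a ground for withdrawal. It is not: the text gives it as a consequence of a surgical-wound problem, and the Safety assessment section has interruptions noted on the next skin assessment form, so interrupted patients are ordinarily expected to stay.

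Nor do the documents tie the surgical wound to open skin under the breast. Failure to heal the wound is already an exclusion criterion, so the example mirrors eligibility. A link with MD risk or its detection is plausible, not shown.

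The five-patient figures are an extreme case, and 50/105 versus 33/110 still gives z of about 2.65 (p about 0.008), so the planned effect would still be declared.

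Finally, staff assessment has a role in the endpoint: a positive PRO counts unless a trained blinded assessor definitively rules MD out. Continued questionnaires do not wholly replace a missed assessment. But the assessor can only overturn a positive report, and staff assessments after radiotherapy are already optional (Table 1), so the outcome can still be scored.

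What remains after these objections is the combination of open discretion, knowledge of the arm, no stated follow-up, and exclusion from the primary analysis.

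**Conclusion.** The concern holds in limited form. As written, the plan permits arm-aware exclusion after randomisation from the primary analysis. It does not show that this will happen often, or more in one arm.

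Under the assumptions used, five would-be MD cases lost from one arm shift a 20-point difference by 2.4 points down or 3.3 points up. With up to 15% withdrawn in an arm, the scenarios give about 3 to 4 points of spurious difference under no effect, in either direction, and up to about 7 points at the planned effect. Equal use at equal risk gives no bias in the difference under no effect, although both observed rates can move.

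It should not be read as a claim that staff will misuse the discretion, that the bias has a known direction, or that the discretion must be abolished. The documents support none of these; the last would reach into clinical judgement when the statistical problem lies in what happens to outcome follow-up.

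**What to change.** Leave clinical decisions, and the discretion to stop study procedures, as they are. Make three changes:

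1. In Participant withdrawal, state that a staff-initiated withdrawal does not end outcome follow-up: weekly PRO questionnaires continue to week 7 from the start of breast radiotherapy unless the patient withdraws consent for follow-up.
2. In Statistical methods – primary outcome, state that these women are analysed in their randomised arm, and that any with a missing outcome enter the imputation analysis already planned.
3. Report staff-initiated withdrawals by arm, reason and date.

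The cost is wording and a few more questionnaire contacts, using the e-mail and remote routes already in place. One small downside is that some positive questionnaires will have no blinded staff assessment that could rule MD out. No change in sample size is needed.

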#### CT simulation

CT simulation will be performed with the patient in supine position for both study arms. The preferred patient position is both arms above the head with elbows resting comfortably on a wing board. Variation in arm position (one arm up) is acceptable if the patient is unable to achieve both arms up. Arm position shall be documented on the treatment planning data sheet. Simulation will be performed using the standard CT protocol at the treating centre, confirmed during the credentialing review. Setup marks will be placed laterally and medially, and tattoos will be applied for future setup at the treatment unit. The preferred method for eliminating patient roll at the time of treatment is to place lateral tattoos on each side of the patient with arms up at the time of simulation. Alternate methods will be confirmed at the time of the credentialing review.

Detailed technical descriptions and figures of CARA are published elsewhere and similar to the completed pilot studies [24–26]. In the experimental arm, CARA settings will be adjusted on a patient-by-patient basis to eliminate the IMF and lateral tissue droop such that that all palpable breast tissue sits anterior to the mid-axilla line. Patient-specific CARA settings will be captured to include in the setup instructions at the treatment unit.

Patients in the control arm will be positioned according to standard practice of care which may include no support, a small foam wedge in the skin fold, a thermoplastic shell, or an alternative supine breast support approved at the time of credentialing review. The method will be recorded with the treatment planning data. No changes to standard practice in the control arm, as reported on the credentialing survey, are permitted during this study without consultation with the steering committee.

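### The only written route off CARA runs through study withdrawal, after which the protocol provides for no outcome collection

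*Protocol article*

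**What the plan says.** All references are to the protocol article; no SAP was available.

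- *Participant withdrawal*, CARA arm: "Patients in the experimental study arm who withdraw from the study will decide, in discussion with the treating oncologist, whether to continue with CARA"; the alternative is a move to standard positioning. A move requires a new CT simulation and plan, which typically takes a week.
- *Participant withdrawal*, control arm: "Patients in the control arm who withdraw from the study post-CT simulation will continue with treatment as planned, with no interruption".
- *Participant withdrawal*, data: "Data collected up to the point of withdrawal will remain in the study". No questionnaire or skin assessment after withdrawal is described.
- *Participant withdrawal*, completion: a completer is someone who is considered to "have completed all phases of the study including treatment and the final PRO questionnaire".
- *Statistical methods – primary outcome*: "Those who do not complete all follow-up and do not report MD will be excluded from the primary analysis". Non-completers who have reported MD stay in. A multiple-imputation sensitivity analysis covers those lost to follow-up.
- *Safety assessment*: the adverse events to be followed up include those that are serious, related to the intervention or study procedures, "or that caused the participant to discontinue the study intervention". This is the one place where stopping the intervention appears as an event separate from withdrawal.
- *CT simulation*: control positioning "may include no support, a small foam wedge in the skin fold, a thermoplastic shell" or another approved supine support.

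**The concern.** Stopping a device and leaving a trial are different events. A woman who finds CARA uncomfortable may still be willing to answer a short weekly questionnaire. If sites follow the text as written, the route they will find for her is withdrawal. She then has no final questionnaire, counts as a non-completer, and is dropped from the primary analysis unless she has already reported MD.

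Either arm can withdraw, and a control patient may also stop using a wedge or shell. However, a move to the other arm's positioning is described only for CARA patients. Loss by that path can occur in one arm only and may be related to the device, so it could distort the randomised comparison. The sensitivity analysis includes the women lost but, by this route, has no outcomes observed after a change of positioning to draw on. No later analysis plan can recover questionnaires that were never sent.

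**Working it through.** **The plan's own figures.** *Sample size calculation and recruitment period* says "we expect a control arm rate of 50% for any degree of MD in the IMF" and hypothesises 30% with CARA, at 80% power and two-sided α = 0.05. With pooled variance:

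n = [1.96·√(2·0.40·0.60) + 0.8416·√(0.25 + 0.21)]² / 0.20² = 93 per arm, as stated. Enrolment is 110 per arm.

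For scale, the standard error of the difference at 110 per arm is √(0.25/110 + 0.21/110) = 0.0647, about 6.5 points.

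**Assumptions (not in the documents).** s = share of the CARA arm that switches by withdrawing, 2–10%. m = their MD risk, from 30% (as for women staying on CARA) to 50% (as for controls). f = share of their MD reported before withdrawal, 0 to 1. Everyone else completes.

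**CARA-arm rate.**

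- All randomised: (1−s)·0.30 + s·m
- Under the primary rule: [(1−s)·0.30 + s·m·f] / [(1−s) + s·m·f]

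Example with s = 0.10, m = 0.50. All randomised: 0.27 + 0.05 = 32.0%. Under the rule: 0.27/0.90 = 30.0% (f = 0); 0.295/0.925 = 31.9% (f = 0.5); 0.32/0.95 = 33.7% (f = 1). Women excluded: 110·0.10·(1 − 0.50·f) = 11, 8.25 and 5.5.

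Error in the CARA rate, in percentage points (rule minus all randomised), with no control loss:

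| s | f = 0, m = 30% | f = 0, m = 50% | f = 1, m = 30% | f = 1, m = 50% |
|---|---|---|---|---|
| 2% | 0 | −0.4 | +0.4 | +0.3 |
| 5% | 0 | −1.0 | +1.1 | +0.8 |
| 10% | 0 | −2.0 | +2.3 | +1.7 |

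Two mechanisms are at work. Losing switchers' outcomes (f = 0) gives an error of −s·(m − 0.30), which favours CARA if switchers are at higher risk than women who stay. Keeping only those non-completers who reported MD pushes the rate up. That second part is the general rule for both arms and is not specific to switching.

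**Equal loss in the control arm** (share s, risk 50%, same f): control rate = [(1−s)·0.50 + s·0.50·f] / [(1−s) + s·0.50·f]. At s = 0.10 this is 50.0%, 51.4% and 52.6% for f = 0, 0.5 and 1. The differences between arms are then:

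- m = 50%: 20.0, 19.5 and 18.9 points against a true 18.0, so CARA is favoured by 0.9–2.0 points.
- m = 30%: 20.0, 20.2 and 20.4 points against a true 20.0, so CARA is favoured by 0–0.4 points.

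**The case against.** The strongest objection is that the quoted sentence covers the care of women who have already left the study and does not make withdrawal a condition of changing position. A reader might infer that every woman who stops CARA is forced out of the trial and lost. The documents do not support that. *Patient population* asks for weekly questionnaires to week 7 with no condition on positioning, completion is not defined by CARA use, and the primary analysis compares the arms without excluding for non-adherence. A switcher who stays on study and keeps responding would be kept. Nor is collection after withdrawal forbidden: the sentence on data is about retention. This part of the objection stands and limits the point.

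Switching may also be rare. *Exclusion criteria* removes women unable to comply with the CARA arm, and a week for re-planning leaves little room in a five-fraction course.

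It can also be said that a journal article leaves analysis sets to the full protocol or SAP. A missing as-randomised statement would indeed be weak on its own. But the article does set out a route off the device, a data cut-off and an exclusion rule, and whether outcomes are collected is a matter of conduct that an analysis plan cannot put right later.

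**Conclusion.** The point holds in a limited form and is a cheap improvement. The text does not force switchers out, but the only route off CARA that it describes passes through withdrawal, provides for no later outcomes, and leads to exclusion from the primary analysis if no MD has been reported.

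Over the assumed ranges, with no control loss, the CARA rate could be up to 2.0 points too low or 2.3 points too high. That is about a third of one standard error at most, and at 2% switching it is no more than 0.4 points either way. The result rests on an assumed switching rate and an assumed risk in switchers; the documents give neither.

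A reader might infer a bias in CARA's favour. The sign is not settled: it depends on how much MD is reported before leaving and on loss in the control arm. Larger figures need switchers to be at higher risk than controls. For example, if 10% switch at 70% risk, none observed, and the all-randomised CARA rate is 30%, the analysed rate is (0.30 − 0.07)/0.90 = 25.6% and the apparent difference 24.4 points. Nothing in the documents supports a risk above the 50% expected with the positioning these women would move to.

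**What to change.** Add to *Participant withdrawal*:

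1. Stopping CARA or changing positioning is not study withdrawal.
2. Such patients continue the weekly questionnaires to week 7 and are analysed in their randomised arm.
3. Study withdrawal is kept for patients who decline further data collection, or whom the investigator withdraws for reasons other than a change of positioning.
4. The date and reason of any change of positioning are recorded in both arms.

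The cost is a wording amendment and one case report form field. Questionnaires after radiotherapy already go out by e-mail.

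The downside is some dilution, because women who changed positioning count in the CARA arm. At 10% switching and 50% risk the expected difference falls from 20.0 to 18.0 points. With all 110 per arm followed, power is then about 78%, against 86% if nobody switches. That is the upper end of the assumed range; at 5% switching the difference is 19.0 points and power about 82%.
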